### Setting

The study was initiated at the Department of Gynecology, Odense University Hospital (OUH), Denmark. The department is one of four national onco-gynecological centers and yearly treat around 400–450 patients with gynecological cancer and borderline disease, of which 70–80 have cervical cancer and 150–160 have endometrial cancer. Overall, about 17% of the patients with cervical cancer, and 60% of patients with endometrial cancer are expected to meet the inclusion criteria (numbers based on the 2016/2017 annual report from DGCD (Danish Gynecological Cancer Database) at dgcd.dk).

### Patient and public involvement

During the study design phase, 10 patient representatives previously treated for cervical or endometrial cancer at the department took part in a 1:1 discussion with [name] or a project nurse about the intervention, the proposed recruitment procedures, the outcomes, and all patient materials including questionnaires and symptom lists used to support patient-provider communication. Revisions were made in accordance. In addition, patient representatives and relatives will be asked to participate in the interpretation and dissemination of the study results.

### Eligibility criteria

All adult women with confirmed early-stage cervical cancer (FIGO stage 1A1–1A2 treated with cone biopsy, loop electrosurgical excision procedure or simple hysterectomy AND no recommendation for sentinel node mapping (tumor < 7 mm)) or low-stage endometrial cancer (FIGO stage 1 endometrioid adenocarcinoma grade 1 and 2 without lymphoid vascular invasion) were invited to participate. All patients were surgically treated at the Department of Gynecology, OUH, were not candidates for oncological treatment pre- or postoperatively, were able to read and speak Danish, and physically and mentally able to participate (Fig. 1).

**Fig. 1 Fig1:**
[figure not shown]
Flowchart

Patients, who did not wish to participate received standard physician-led, need based follow-up, which was implemented as the standard follow-up program during the autumn of 2017.

### Randomization and blinding

The allocation sequence of the randomization is computer-generated with varying block sizes. Block sizes are kept unknown for all investigators. Due to the study design, patients and clinicians involved in the treatment are informed about allocation status. During data processing and statistical analyses, the statistician and the research group will be blinded.

### Participant timeline, recruitment, and allocation

From March 2019, patients were consecutively invited to participate in the study at the prescheduled encounter 3–4 weeks after primary surgery.

All patients (i.e., patients in the intervention group and in the standard treatment group) follow the same follow-up trajectory during the first four months after surgery (Fig. 2), which include:*A nurse-led consultation 3–4 weeks* after primary surgery, including in-consult needs assessment led by the nurse using a one-paged tick-off list of the most common physical and psychosocial problems after cancer treatment. Further, symptoms and other post-operative sequelae are reviewed using a disease specific list of alarm symptoms prepared by working groups of the Danish Gynaecological Cancer Group (DGCG) [42], and the patient is carefully instructed to be aware of and contact the department in case of symptoms from the list as they may indicate recurrence. Patients are reassured that access to clinical examination is available and provided when needed during the entire follow-up period (up to 3 years after primary surgery).At this time, disease stage and indication for adjuvant therapy has been clarified, and patients who meet the inclusion criteria will be given oral and written information about the project by the project nurse. Participants give their written consent. Next, the nurse creates a case report in the REDCap (Research Electronic Data Capture) system and enter basic information about the patient. A randomization button will appear, and the randomization is carried out using the Randomization Module within REDCap. The patients are informed about their randomization status by the nurse.In the rare case a patient fails to attend this consultation, the nurse will call the patient and make another appointment. This procedure ensures that most eligible patients will be given the opportunity to receive information about the study.*A follow-up consultation with a physician 4 months postoperatively*, where a clinical assessment is performed, and ‘the preparatory form’ and ‘symptom list’ are reviewed as part of the need assessment. In case the symptom report or the clinical examination indicate potential persistent disease, the patient is excluded from the study. Otherwise, the next encounter in their follow-up is planned in accordance with their allocation status and needs. The patients in the intervention group are scheduled for a nurse-led consultation, most often by phone, and patients in the control group are scheduled for a physician-led consultation at the outpatient clinic.

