**Fig. 4 Fig4:**
[figure not shown]
SPIRIT schedule of enrolment, interventions, and assessments

The primary outcome is change in patient empowerment from baseline to 12 months as measured by the Skill and technique subscale of the validated Health Education Impact Questionnaire (HEI-Q) [59, 60]. The HEI-Q was developed to assess the effects of health education programs on self-management among individuals with chronic conditions, including cancer [59], and has been validated in Danish [61]. The 40-item questionnaire comprises five subscales each conceptualized as key aspects of patient empowerment, including social integration and support, health service navigation, constructive attitudes and approaches, skill and technique acquisition, and emotional distress. The skill and technique acquisition construct aims to capture the knowledge-based skills and techniques that persons acquire (or re-learn) to help them cope with symptoms and health problems, which was found essential in order to evaluate the intervention, and therefore chosen as the primary outcome.

The secondary outcomes include fear of cancer recurrence (Fear of Cancer Recurrence Inventory, FCRI) [62], patient involvement (CollaboRATE) [63], health status (EQ5D) [64–66], and Quality Of Life (EORTC QLQ C30) [43] including disease-specific late effects using the QLQ-CX24 module [44] for cervical cancer and the QLQ-EN24 [45] for endometrial cancer. The baseline questionnaire furthermore obtained information on socio-demographic characteristics: education, employment status, income, cohabitant status, comorbidity, height/weight (BMI), and smoking status.

Data from the National Patient Register and the Danish Pathology Register regarding disease-free survival (DFS) and disease recurrence (IDR) will be obtained for all patients after 3 and 5 years of follow-up.

Further, the number, type, and duration of all contacts to the department in the two groups are registered and, in combination with the five questions about health status of the EQ5D questionnaire [66], used to calculate QALYs at a health economic evaluation of cost-effectiveness 5 years postoperatively.

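### Randomised patients are excluded at the 4-month visit on suspicion of persistent disease, with the arm known, so the comparison is no longer as randomised and their place in the recurrence data is unclear

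*Protocol article*

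**What the plan says.** The sequence is set out in the protocol article under Participant timeline, recruitment, and allocation.

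- Entry: "patients were consecutively invited to participate in the study at the prescheduled encounter 3–4 weeks after primary surgery". Consent is taken at that visit.
- Allocation follows at once: "A randomization button will appear, and the randomization is carried out using the Randomization Module within REDCap". Then: "The patients are informed about their randomization status by the nurse".
- Next comes "A follow-up consultation with a physician 4 months postoperatively", at which symptoms are reviewed and the patient is examined. The rule at this visit is: "In case the symptom report or the clinical examination indicate potential persistent disease, the patient is excluded from the study". For everyone else, the next contact is planned according to allocated arm.
- Until that point both arms "follow the same follow-up trajectory during the first four months after surgery".

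Under Randomization and blinding, "patients and clinicians involved in the treatment are informed about allocation status".

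The Outcomes section promises that register data on "disease-free survival (DFS) and disease recurrence (IDR) will be obtained for all patients after 3 and 5 years of follow-up", and the Discussion repeats that recurrence will be assessed in everyone at those two times. Neither place says whether patients removed at 4 months are included.

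**The concern.** Eligibility is settled and the arm assigned before this rule operates, so it is an exclusion after randomisation. It is written into the plan as a rule; it is not a detail left open for a later document.

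Three features make it more than a formality. The trigger needs judgement, since either the patient's symptom report or the examination is enough, and the disease need only be potential. Both people who supply that information know the arm. And the physician decides at the visit where the next step differs by arm: mostly nurse telephone contact in one, and face-to-face consultation with gynaecological examination and transvaginal ultrasound in the other. The threshold for calling a finding suspicious, or for mentioning a symptom, could therefore differ between arms.

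At stake are the as-randomised basis of every between-arm comparison and the completeness of the disease-free survival count. Patients removed for suspected persistent disease are the ones most likely to contribute early events to that count.

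**Working it through.** **1. Time from randomisation to exclusion.** Four months at 30.4 days is 121.6 days. Subtracting 28 or 21 days leaves 93.6–100.6 days, which is 3.1–3.3 months.

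**2. The plan's own sample size.** Inputs from the Sample size section: scale SD 0.43, multiplied by √2 for change; effect 0.21; type I error 0.05 (two-sided assumed); power 80%.

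- SD of change = 0.43 × √2 = 0.608.
- n per arm = 2 × [0.608 × (1.960 + 0.842) / 0.21]² = 131.6, so 132 per arm and 264 in total. The t-test version gives 133 per arm and 266 in total. The stated 268 is close to both.
- 134 / 0.70 = 191.4, so 192 per arm and 384 in total, as stated.

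The sample size reproduces and is not in dispute.

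**3. Effect on power.** The number excluded at 4 months is not given, so the shares below are assumed. Each is taken on top of the planned 30% attrition. Power = Φ(0.21 / [0.608 × √(2/m)] − 1.96), where m is completers per arm.

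| Share excluded | Patients of 384 | Completers | Power |
|---|---|---|---|
| 0% | 0 | 268.8 | 80.8% |
| 1% | 4 | 266.1 | 80.4% |
| 2% | 8 | 263.4 | 80.0% |
| 5% | 19 | 255.4 | 78.8% |

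**4. Effect on the primary contrast.** Bias ≈ (f₁ − f₀) × g. Here f₁ and f₀ are the shares excluded in each arm, and g is how far the excluded patients' mean change differs from that of the retained patients. All values are assumed; g is set at the target effect (0.21) or one scale SD (0.43).

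| f₁, f₀ | g = 0.21 | g = 0.43 |
|---|---|---|
| 1%, 1% | 0 | 0 |
| 2%, 0% | 0.0042 | 0.0086 |
| 3%, 1% | 0.0042 | 0.0086 |
| 5%, 2% | 0.0063 | 0.0129 |

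The non-zero results are 2–6% of 0.21 (0.0042/0.21 = 2%; 0.0129/0.21 = 6%).

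**5. Exposure of the recurrence and disease-free survival data.** Inputs: recurrence 8.5% (endometrial) and 1.6% (cervical), from Harms; yearly cases 150–160 and 70–80, with 60% and 17% eligible, from Setting.

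- Eligible per year: endometrial 90–96, cervical 11.9–13.6, so 87–89% are endometrial.
- Pooled risk: lowest 0.869 × 0.085 + 0.131 × 0.016 = 7.6%; highest 0.890 × 0.085 + 0.110 × 0.016 = 7.7%.
- Expected in 384: about 29–30, or roughly 15 per arm.
- If 5–20% as many events as this (assumed) were removed at 4 months, about 1.5–6 would be lost. Each event counted or left out moves one arm's proportion by about 1/192 = 0.5 percentage points.

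Persistent disease is not the same as recurrence, and the article gives no time horizon for the two rates. This step shows how sparse the events are. It does not predict the loss.

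**6. The passages side by side.** The timeline section takes some randomised patients out of the study. Outcomes and Discussion promise register data on everyone. The section on modifications or discontinuation handles a later recurrence in the intervention arm with a doctor's evaluation and a new plan, and does not mention removal from the study. The article does not say which statement governs a patient suspected at 4 months.

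**The case against.** The best defence is that care is planned to be identical until 4 months and the detecting visit is the same in both arms. Nurse-led follow-up under the intervention has not started, so treatment received cannot cause the exclusion. Imbalance can arise only through judgement or symptom reporting with the arm known, and the document gives no evidence of how large that is. The register data do not depend on questionnaire participation, so the promise to cover everyone may already include these patients. Analysis sets are also commonly defined in a statistical analysis plan, which is not shown here.

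Much of this stands. It limits the size of the problem and turns the recurrence issue into an ambiguity, not a proven loss. It does not remove the point, which rests on a stated exclusion rule and not on the lack of an analysis-set definition. A sentence making clear that excluded patients still count would be needed even on the favourable reading.

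A reader might go further in three ways that the document does not support:

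- That the arms become non-comparable for the primary outcome. Identical early care and the 2–6% shift in step 4 speak against this.
- That a large fraction of expected recurrences is deleted. This needs an invented exclusion rate, needs nearly every suspicion to be confirmed, and divides persistent disease by recurrence.
- That the rule undermines the only safety comparison of telephone follow-up. Disease found at 4 months is found before the arms diverge and by the same procedure, so it says little about what telephone contact misses. The Harms section also plans to investigate recurrences in both groups and to measure fear of recurrence.

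**Conclusion.** The point holds in a limited form. The plan removes randomised patients about 3 months after allocation, on suspicion, with the arm known to patient and clinician, so the remaining comparison is not as randomised. It also leaves open whether these patients enter the recurrence and disease-free survival data.

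The likely effect on the primary outcome is small: a shift of 0.004–0.013 points, and power between 78.8% and 80.4% for 1–5% excluded. Both ranges rest on assumed exclusion shares, and the shift also on assumed differences between excluded and retained patients. The more exposed quantity is an as-randomised disease-free survival count, where early events could be lost from a total of about 29–30 expected recurrences. That outcome is neither primary nor powered. The correction is still worth making, because it is cheap and follow-up that has lapsed cannot be recovered later.

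**What to change.** Replace the exclusion clause at the 4-month visit with wording to this effect: if persistent disease is suspected, the care pathway is decided clinically, as now, and the patient remains in the analysis set of her allocated arm, with the finding recorded as an intercurrent event.

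Then, where consent allows:

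- keep sending the questionnaires still due at 12, 18 and 36 months;
- use the 3-month baseline and any later data already collected;
- include her in the register-based recurrence and disease-free survival comparison at 3 and 5 years.

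Report the number of such cases by arm, and reconcile the timeline section with Outcomes and Discussion by stating that register follow-up covers every randomised patient. Apply the same to patients already excluded, as far as consent permits.

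The cost is protocol wording and a few extra questionnaires; clinical management does not change. One loss cannot be repaired. Inclusion began on 1 March 2019, so for patients excluded early the 12-month questionnaire window has passed and their primary outcome stays missing. For them the remedy is limited to existing data, register follow-up and reporting by arm.

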
**Fig. 2 Fig2:**
[figure not shown]
Timeline; 6 examples

#### The control group

The physician-led usual care program consists of out-patient face-to-face consultations including a gynecological examination and a transvaginal ultrasound examination and scheduled based on individualized need assessment. At the end of each consultation, the patient and the physician agree on if or when to schedule a new consultation based on the needs of the patient and guided by disease-related needs, sequelae after surgery, compliance, comorbidity, and other relevant factors.

#### The intervention group

The nurse-led model is led by a project nurse and based on phone contacts with content and intervals individually planned in agreement with the patient. In some cases, attendance in the outpatient clinic may be preferred by the patient or by the project nurse, i.e., in case of complex supportive care needs or when active involvement of a relative is considered essential for the empowerment process.

During encounters, the nurse will be supported by graphic visualization of the results of the ePROMs completed in REDCap by the patient before each contact. The ePROMs include a disease specific symptom list and the generic European Organization for Research and Treatment of Cancer Quality of Life Questionnaire (EORTC QLQ-C30) [43] supplemented with the relevant disease-specific add-on questionnaire modules (EORTC EN24 or EORTC CX24) [44, 45]. Thresholds for the scores are pre-defined and visualized to health professionals with colors to indicate severe problems (red), no problems (green) and mild or moderate problems (yellow and orange), respectively. Hence, alarm symptoms and problem areas are clearly presented to the nurses and changes over time can be visualized thus improving the interpretation. This feature of the REDCap is comparable to that of the AmbuFlex technology [46], which has been used for similar projects in lung, prostate, breast, and gynecological cancer settings [47–50].

Each consultation includes:Review of the PROM in collaboration between clinician and patient with specific attention to alarm symptomsDialogue facilitating identification and utilization of available resources (own, relatives, general practitioner, supportive care activities in the local municipality, and in the local community in general)Support of patient empowerment and self-managementReferral to relevant support if neededReferral to medical examination if neededShared decision of time and target of future follow-up

At the end of each consultation, the patient and the nurse agree on if and when to schedule a new consultation.

#### Duration of the programs

Both follow-up programs have a maximum duration of 3 years, regardless of allocation status. All patients in both groups may at any time request to end their formal follow-up. In this case, no new contact is planned, but the patient can contact the department directly in case of symptoms or worry for up to 3 years after surgery.

#### Modifications or discontinuation of the intervention

If a patient in the intervention group wish to withdraw their consent or in the rare case of recurrence, the patient will be evaluated by a doctor and a plan for future follow-up or further investigations will be made. There are no restrictions regarding concomitant care during the trial.

### Training of the project nurses

A total of six project nurses were trained to lead the intervention group consultations. The training program was based on theories about professional learning (knowledge, role-play and supervision may enable professionals to change clinical behavior), health communication, the bio-psycho-social understanding of diseases like cancer, and holistic needs assessment (includes the variety of problems and needs that may follow cancer treatment).

The training program included a pre-study 2-day seminar and brush-up training during the study period. The project nurses were all experienced within the onco-gynecological field from years of engagement in the department and had applied for the position as project nurse specifically on this project.

The training at the 2-day seminar was led by chief psychologist [name] who is specialized in rehabilitation and empowerment of cancer patients. Experienced medical physicians and psychologists provided a mixture of interactive lectures and role plays with a professional actor as the patient. The theoretical themes were empowerment, adjustment psychology, and benefits and risks when using PROMs as dialogue support tool. Further, the educational program included medical aspects of endometrial and cervical cancer with special attention to alarm symptoms, recurrence, late effects and normal physical, social and psycho-sexual reactions, and problems related to gynecologic cancer. The clinical cases used for role play were described as difficult situations by the project nurses or by the study physicians ([name] and [name]) beforehand and were reviewed with psychological aspects by the course leader.

Brush-up training is planned annually during the inclusion period and will be supervised by [name] and [name].

### Theoretical frameworks for the intervention

This nurse-led intervention and the teaching program to nurses were designed based on theories about (1) empowerment as an important component in enabling people in handling (nurses are empowered and patients are empowered), (2) attachment as a way to understand the individual patient ‘s behavior and trust in clinical consultations and professional relationships, and (3) PROM in the clinical consultation as a relevant dialogue tool (conceptualizes to patients and professionals what may be relevant issues and serves as a method to target delivery of supportive care in line with the patient’s needs).

The theoretical frame of the intervention is summarized in the logic model (Fig. 3). The logic model visualizes the assumptions and theory of action that underlie the structure of the intervention, and it defines the four components of the models: resources, activities, outputs, and outcomes, and explains how they connect.Theoretical framework of empowermentA central part of the program was to support the empowerment of patients in a relational context. Lately, more attention has been given to how to encourage the patients to handle their own supportive care process, i.e., how to optimize the empowering processes supported by the health care providers [51]. It is acknowledged that the health care providers play an important role in encouraging, accepting and enabling the patient to be empowered [51], for example, by providing adequate information to the patients on how to navigate. However, it is important to note that there is not a direct link between the enabling of empowerment and empowerment outcomes. Thus, the empowerment of the patient is a process pending on the relationship between the patient and the health care provider but also involves the patient’s relatives, her network, her general practitioner, local supportive care activities, and her motivation for being empowered.Theoretical framework of attachment in the clinical contextUnderstanding the patient’s premises of trusting clinicians is crucially important for the clinician’s ability to support the patient during cancer follow-up. Attachment theory explains differences in close relationships under threatening circumstances, as in this case, a cancer diagnosis [52]. By applying this theory, often held assumptions such as “everybody wants information” or “it is always good to talk about emotions” were discussed and nuanced. In accordance, theory about attachment styles and how to understand different attachment orientations during clinical encounters was part of the educational training of the project nurses.Theoretical framework of PROM as a dialogue supportive tool

